# START NOW WebApp—promoting emotion regulation and resilience in residential youth care and correctional institutions: study protocol for a cluster randomized controlled trial

**DOI:** 10.1186/s13063-024-08180-z

**Published:** 2024-05-22

**Keywords:** Randomized controlled trial, Intervention, Adolescents, Young adults, Residential youth care, Emotion regulation, Psychological flexibility, Resilience

## Abstract

**Background:**

Adolescents and young adults in residential care and correctional institutions face various challenges, leading to negative life outcomes. Implementation barriers within these institutions, such as limited financial and spatial resources, pose significant hurdles to providing necessary support. Web-based approaches address these challenges by offering cost-effective, accessible solutions. This study aims to assess the efficacy of a newly developed web-based version of the existing evidence-based START NOW skills training in fostering emotion regulation and resilience among institutionalized adolescents and young adults. We present the study protocol (Version 5, August 2023) of the trial titled “Implementation of an e-version of the skills training START NOW for promoting emotion regulation and resilience in residential youth care and correctional institutions”.

**Methods:**

The study is a monocentric, prospective, confirmatory randomized controlled trial with 150 institutionalized adolescents and young adults with a need to improve resilience (predefined cut-offs). Participating institutions will be randomized to one of three conditions: (i) 9-week web-based group training guided by a facilitator, (ii) 9-week web-based self-help training, (iii) and treatment as usual. The primary endpoint is the change in psychological flexibility, assessed by the Avoidance and Fusion Questionnaire for Youth score, from baseline to follow-up 12 weeks post skills training. Secondary objectives encompass assessing pre-post changes in psychological flexibility and other psychological health-related outcome measures in participating adolescents, young adults, and caretakers from baseline, to post training, and to 12- and 24-week follow-ups.

**Discussion:**

This study evaluates the efficacy of START NOW as web-based training for institutionalized adolescents and young adults, providing valuable insights into web-based interventions and aiming to optimize support levels.

**Trial registration {2a and 2b}:**

ClinicalTrials.gov NCT05313581. Registered on 6 April 2022.

**Supplementary Information:**

The online version contains supplementary material available at 10.1186/s13063-024-08180-z.

## Introduction

### Background and rationale {6a}

Numerous studies on adolescents and young adults (AYA) indicate a much higher rate of mental health problems in residential youth care (RYC) and correctional institutions (CI) than in the general population [1, 2]. The presence of risk factors (such as impulsivity, no family/social support, emotion regulation deficits) further exacerbates an AYA’s risk for negative life outcomes [3, 4] with staggering costs to society [5, 6]. In general, the burden in affected children and AYA is extremely high, emphasizing the need for innovative, tailored approaches to bring evidence-based care to settings with limited resources [7–10].

START NOW is one integrative approach well-suited for settings with resource constraints and an extensive need for effective, reliable treatment for individuals exhibiting impairments in emotion regulation and management of social competencies [11]. The intervention comprises a manualized skills training with mindfulness exercises, functional analyses of emotion and behavior, as well as, specific topics such as accepting emotions, building up interpersonal skills, and setting goals, thus promoting general psychological health and resilience. START NOW facilitators undergo a training providing background information on basic aspects of cognitive behavioral therapy (CBT), motivational interviewing (MI), dialectical behavior therapy (DBT), acceptance and commitment therapy (ACT), and trauma-sensitive care, as well as practical exercises on how to facilitate the skills training [12]. There is accumulated support for the use of the START NOW intervention with adult forensic and correctional populations, institutionalized AYA as well as student populations. Indeed, studies have shown START NOW’s effectiveness in terms of reduced behavioral problems [13], reduced hospitalization rates [14], improved mental health functioning [15] and high satisfaction rates [16]. In addition, Stadler et al. [17] adapted START NOW for AYA and investigated its implementation and efficacy within an international randomized trial. Results demonstrated START NOW`s effectiveness in reducing aggressive and oppositional behaviors in institutionalized AYA.

However, challenges persist in implementing skills training programs in RYC and CI, such as institutional or personal constraints (staff shortage, high staff turnovers, working in shifts), as well as constraints in AYA (limited time or motivation, discharge/transfer of institution), ultimately limiting the effectiveness of such programs [18, 19]. Web-based approaches, delivering health services on various devices, offer promising solutions to outlined implementation barriers, providing cost-effectiveness, high accessibility, flexibility, direct resource utilization, anonymity, reduced stigma, and a practical means for ensuring continuity of care during transitional phases [20, 21].

The effectiveness of web-based health approaches is well established across settings, populations (e.g., non-clinical, clinical, adolescents, adults), and a range of mental health outcomes, such as improvement of clinical symptoms, mindfulness, and quality of life/well-being [22–25]. Studies directly comparing the efficacy of face-to-face and web-based approaches show no significant differences between the two approaches [26–28]. Yet, web-based approaches can vary substantially in their delivery format ranging from unguided self-help services to guided services (human support mostly through tailored, written feedback) to real-time, direct human support through, for example, videoconferencing or telephone services. With regard to specific delivery format, the efficacy of web-based approaches increases with the extent of support: Web-based approaches including human support come with larger effects and greater adherence compared to unguided self-help and tend to be as effective as face-to-face intervention formats [29–32].

Thus, the current study aims to investigate whether a web-based version of START NOW—with or without additional support—is effective in enhancing psychological flexibility (PF), a core indicator of good mental health and resilience [33–36]. Additionally, through qualitative interviews, we will investigate whether web-based applications are suitable for overcoming given constraints, consequently, contributing to a better and more sustainable implementation of evidence-based care in RYC and CI.

### Objectives {7}

This project aims to evaluate a web-based translation of the existing START NOW skills training that promotes resilience and emotion regulation, operationalized through PF, in institutionalized AYA, while addressing the numerous barriers to program implementation in the RYC and CI settings. We will investigate the efficacy of a web-based version of START NOW on PF in a randomized controlled trial comparing the following conditions: (1) web-based group training guided by a facilitator (trained START NOW facilitator, providing guidance through sessions and motivating change), (2) web-based self-help training (without guidance, with automated feedback responses), and (3) treatment as usual (TAU). In accordance with the literature, we expect to see the largest effect on PF within the web-based group training guided by a facilitator. PF and respective inflexibility will be assessed by the change in self-rated Avoidance and Fusion Questionnaire for Youth (AFQ-Y) [37] score from baseline to follow-up (12 weeks post skills training).

#### Hypotheses

In institutionalized AYA web-based START NOW skills training is more efficient when delivered as group training guided by a facilitator (motivates to change behavior) than TAU in decreasing psychological inflexibility (primary outcome) as measured by AFQ-Y scores 12 weeks ± 2 weeks (T_3_) after the end of the intervention.

Statistical hypothesis:H_0_: 12 weeks after the end of the intervention (at T_3_), mean inflexibility, as assessed by the Avoidance and Fusion Questionnaire for Youth (AFQ-Y), is not different in participants receiving TAU and in participants receiving a web-based START NOW training.H_a_: 12 weeks after the end of the intervention (at T_3_), mean inflexibility, as assessed by the Avoidance and Fusion Questionnaire for Youth (AFQ-Y), is different in participants receiving TAU and in participants receiving a web-based START NOW training.

2)In institutionalized AYA START NOW skills training is more efficient when delivered as web-based self-help training than TAU in decreasing psychological inflexibility (primary outcome) as measured by AFQ-Y scores 12 weeks ± 2 weeks (T_3_) after the end of the intervention.

#### Secondary objectives

The skills training is expected to improve general resilience and decrease depression and anxiety symptoms, and irritability [13, 17]. Building on this, the START NOW skills training in a group guided by a facilitator may be more effective than self-help web-based training and TAU in enhancing resilience, self-efficacy, well-being, and reducing impairment, depression, anxiety, and irritability. In addition, different covariates and potential moderators including gender, age, access to the internet, caretaker/facilitator, or institutional criteria will be investigated. A positive social climate has been associated with positive outcomes, such as motivation for the intervention, active use of skills, greater intervention satisfaction and resilience, and fewer problem behaviors, such as bullying, aggression, or social problems [38]. Therefore, the moderating effect of the social atmosphere within the institution will also be examined. Former positive feedback from personnel trained in START NOW [17] lead to the hypothesis, that caretakers completing START NOW facilitation courses will exhibit improved resilience, with greater gains in the group training condition compared to self-help and TAU. Gains are linked to better insights, improved self-efficacy, and more opportunity for positive exchanges with youth. The caretakers’ level of resilience, as caretakers in the active intervention conditions will partake in a START NOW training course, will be examined in the study. Furthermore, participants’ and caretakers’ satisfaction with the training will be evaluated.

### Trial design {8}

The study is a monocentric, prospective, confirmatory randomized controlled trial with three experimental conditions: (1) START NOW as web-based group training guided by a facilitator, (2) START NOW as web-based pure self-help training, and (3) TAU. Institutions are randomly assigned 2 weeks before the 9-week intervention phase.

## Methods: participants, interventions, and outcomes

### Study setting {9}

The study is conducted by the Department of Child and Adolescent Psychiatry, University Psychiatric Clinics Basel. Data is collected in RYC a CI recognized by the Federal Office of Justice (FOJ) [39] throughout the German and French-speaking parts of Switzerland. Assessments are conducted at five time-points (T). First to screen for eligibility (T_0_), then before intervention start (T_1_), immediately following intervention end (T_2_), 12 weeks ± 2 weeks after intervention end (T_3_), and 24 weeks ± 2 weeks after intervention end (T_4_).

### Eligibility criteria {10}

Inclusion criteria are listed in Table 1.

**Table 1 Tab1:** Eligibility criteria for institutions and participants

Inclusion criteria for institutions:	Inclusion criteria for participants:
• Institutional consent • Ability to offer a 9-week group training guided by a facilitator • At least two designated START NOW trainers that successfully complete the full 1.5 days of training • Internet access for participants • Guarantee of standardized implementation	• AYA in RYC or CI • Ages 14 to 24 years • Sufficient German or French language skills • Participant consent • AFQ-Y sum score ≥ 34.05 • MAYSI-2 subscale angry-irritable sum score ≥ 5.0 • MAYSI-2 subscale depressed-anxious sum score ≥ 3.0 • No concurrent group-based skills training

*Note. AYA* adolescents and young adults*; AFQ-Y* Avoidance and Fusion Questionnaire for Youth; *MAYSI-2* Massachusetts Youth Screening Instrument-2. Participants with high scores on MAYSI-2 subscales Suicide-Ideation (≥ 2) or Thought-Disturbance (≥ 2) are individually assessed with caretakers. Suicidal or otherwise acutely endangered participants are excluded

### Consent or assent {26}

#### Who will take informed consent? {26a}

A trained member of the START NOW study team provides information about the study, including study procedures and informed consent, to all interested participants (in-person or online). Consenting AYA fill out a physical consent form. Forms are checked by the research team and filed in a secure location before participation is approved.

#### Additional consent provisions for collection and use of participant data and biological specimens {26b}

Not applicable, as no biological specimens are collected in this study.

### Interventions {11}

#### Explanation for the choice of comparators {6b}

We will evaluate the efficacy of web-based START NOW on PF in a randomized controlled trial with three conditions: (1) web-based group training guided by a facilitator, (2) web-based self-help training, and (3) TAU. The inclusion of guided group training aims to assess the benefits of facilitator support, examining its potential superiority in delivering START NOW. Incorporating a self-help approach considers the resource implications of human-supported interventions, exploring the standalone effectiveness of START NOW. TAU acts as a control condition to isolate and assess specific impacts of the START NOW Web Application (WebApp). In summary, our chosen comparators systematically assess the effectiveness of web-based START NOW, considering human support advantages, resource implications, and the need for a relevant control group.

#### Intervention description {11a}

The WebApp is based on the manualized START NOW skills training. Each session is structured and comprises mindfulness exercises, functional analyses of emotion and behavior, as well as specific topics such as accepting emotions, building up interpersonal skills, and setting goals. Content is available in German and French across 12 sessions, incorporating gender-inclusive elements. It employs comics, video clips, and various exercises. Participants can track their progress, collect trophies, and have the option to become co-trainers by the end of the intervention. The WebApp aligns with Good Clinical Practice Guidelines and was validated by the Department of Clinical Research (DCR), University of Basel, and University Hospital Basel. Throughout the 9-week intervention phase, START NOW sessions unlock weekly with sessions 1 and 2, 9 and 10, and 11 and 12 being double sessions. The sessions are conducted either a) as 12 web-based group trainings (4 to 12 participants) guided by a facilitator (face-to-face or videoconferencing; duration 60 min; 120 min for double sessions), or b) as self-help training (duration 45 +/- 15 min; 90, +/− 15 min for double sessions). All participants have access to the START NOW WebApp during the entire intervention and follow-up phase to complete additional exercises or review content. Sessions will be unlocked on a weekly basis to keep the schedule between conditions consistent. Participants will receive reminders about unlocked sessions, though they may ignore the overall session order and may finish unlocked sessions out of order. Additionally, participants will be able to repeat content of previous sessions, to do bonus assignments for themselves, and to contribute to a forum. Participants of the TAU conditions will be provided with web-based self-help training after completion of the study. Facilitation will be provided either by a trained staff member (caretaker) of the institution or by a member of the START NOW facilitator team of the University Psychiatric Clinics (UPC) Basel (videoconference setting). The 12 h START NOW training for RYC/CI staff members covers session content and facilitation and includes background information on the core elements of the intervention: MI, CBT, DBT, and trauma-sensitive care.

#### Criteria for discontinuing or modifying allocated interventions {11b}

Any participant can withdraw their consent for the study at any time. The principal investigator and the Basel study team can also decide about termination of intervention for individual participants: in case of adverse events (AE), or if, in the investigators’ opinion, continuation in the investigation would be detrimental to the participants’ well-being. The date of withdrawal is to be documented. The Ethics Committee (EC) and the competent authorities must be informed about premature closure of the trial or one of the intervention arms. Furthermore, the EC(s) and competent authorities themselves may decide to stop or suspend the trial.

#### Strategies to improve adherence to interventions {11c}

To ensure standardized implementation by facilitators, participating staff will be adequately trained. Also, the quality of the group training guided by a facilitator will be rated by a research team member during the second session (either live or via online connection) using a Quality Assurance Form [40]. Supervision for participating caretakers and facilitators (except TAU condition) will be provided twice during the intervention phase: First time immediately after the second session, the second time in the first half of the intervention (2 h per session). Moreover, caretakers and facilitators can reach out via e-mail to assigned START NOW study coordinators for further guidance. The purpose is to assist caretakers and facilitators in the realization of START NOW, to cope with difficult situations, to progress in expertise, as well as to ensure good service to the participants. After every session of the group training, attendance of the participants will be assessed via e-mail or phone with the responsible trainer.

Participants will be compensated with online shopping vouchers for participating in questionnaires (CHF 20 for one completed time-point). They can additionally earn a special co-trainer certification after completing the full training. Additionally, all web-based training aspects allow collection of virtual coins, medals, or diamonds (depending on the activity) which are displayed on a progress screen. Participants are also reminded regularly about new and not yet finished sessions.

The material also highlights the potential benefits for participants, addressing the possibility of better stress and emotion management and encouraging self-efficacy.

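### Self-help versus TAU tests the WebApp together with START NOW-trained and supervised staff, so it cannot isolate the WebApp or show standalone effectiveness as section {6b} says

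*Protocol article*

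**What the plan says.** Section {6b} of the protocol article gives each comparator a purpose. The self-help arm is justified as "exploring the standalone effectiveness of START NOW". For the control arm it says "TAU acts as a control condition to isolate and assess specific impacts of the START NOW Web Application (WebApp". Trial design {8} names the second arm "START NOW as web-based pure self-help training", and Objectives {7} describes it as "web-based self-help training (without guidance, with automated feedback responses".

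Other sections describe what staff receive:

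- Secondary objectives: "caretakers in the active intervention conditions will partake in a START NOW training course". This covers the guided group arm and the self-help arm alike.
- Intervention description {11a}: "The 12 h START NOW training for RYC/CI staff members covers session content and facilitation". The course also gives background on the therapeutic elements behind the programme.
- Adherence strategies {11c}: "Supervision for participating caretakers and facilitators (except TAU condition) will be provided twice during the intervention phase". Each supervision lasts 2 h, and e-mail contact with study coordinators is available as well. The stated aim is to help staff put START NOW into practice.
- Recruitment {15}: TAU institutions receive training and WebApp access only after follow-up II (T4).
- Eligibility {10}, Table 1: every institution must have at least two designated trainers who complete 1.5 days of training. TAU is not exempted.

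**The concern.** Self-help versus TAU on the AFQ-Y at T3 is the second hypothesis on the primary outcome. If the arms differ both in WebApp access and in whether staff are trained and supervised in the same skills, the contrast measures the two together. The comparator rationale in {6b} promises something narrower: the WebApp's specific effect, and effectiveness standing alone.

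The distinction matters because the background section presents web delivery as an answer to staff shortage and turnover. A reader who takes {6b} at its word could conclude from a positive result that the WebApp works without staff input. The trial has no arm that tests this. The Limitations section does not mention it.

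**Working it through.** **Step 1. What each arm has before the T3 endpoint, as written.**

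| Component | Guided group | Self-help | TAU |
|---|---|---|---|
| WebApp ({11a}, {15}) | yes | yes | no |
| Facilitator in sessions ({7}, {11a}) | yes | no | no |
| Staff START NOW course (Secondary objectives, {15}) | yes | yes | no |
| Two staff supervisions ({11c}) | yes | yes | no |

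**Step 2. What the contrasts estimate.** Write W for the WebApp effect, F for the session facilitator and S for the staff course and supervision. Assume for simplicity that they add.

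- Guided group minus TAU = W + F + S
- Self-help minus TAU = W + S
- Guided group minus self-help = F

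The rows for the WebApp and for supervision are identical (yes, yes, no), so W and S cannot be separated. The primary model in {20a} has arm and baseline AFQ-Y as fixed effects. Adding a covariate would not help, because the planned staff component is fixed by arm.

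**Step 3. The other reading of TAU training.** If Table 1 is taken literally and TAU trainers are also trained before T3, the course row becomes (yes, yes, yes) and drops out of the TAU contrasts. The supervision row stays (yes, yes, no). The conclusion then holds for a smaller staff component.

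**Step 4. Size.** The documents give no figure for a staff effect. The following is an illustration with assumed values only.

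*Reproducing the plan's figure.* Sample size {14} states 26 effective participants per condition, d = 0.50 for self-help versus TAU, r = 0.80 and 80% power. It states no alpha; two-sided 0.05 is assumed. With change scores, the variance in SD² units is 2 × (1 − 0.80) = 0.40. Then n = 2 × (1.96 + 0.84)² × 0.40 / 0.50² = 25.1, which rounds up to 26, as stated. Power at 26 is 0.813.

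*Illustration.* Suppose W = 0 and only the staff component acts. The standard error is √(2 × 0.40 / 26) = 0.175. The chance of a significant result favouring self-help is P(Z > 1.96 − d/0.175); with no effect at all it would be 0.025.

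| Assumed staff effect d | AFQ-Y points (d × 13.01) | Chance of a significant result favouring self-help |
|---|---|---|
| 0.1 | 1.3 | 0.08 |
| 0.2 | 2.6 | 0.21 |
| 0.3 | 3.9 | 0.40 |

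These would be correct rejections for the package. They would be wrong only if credited to the WebApp.

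**The case against.** The case for leaving the text alone has real weight.

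- *The arm labels are defensible.* Objectives {7} ties guidance to a facilitator leading sessions, and the background contrasts unguided self-help with human support given to the user. No section says caretakers coach self-help participants. A reader might infer that 'pure' and 'without guidance' are contradicted by the staff course. The documents do not support that, provided the terms mean no facilitator in sessions.
- *Hypothesis 2 is answerable.* It concerns START NOW delivered as self-help against TAU, and randomization by institution answers exactly that. This stands.
- *The protocol does not claim that trained staff change youth AFQ-Y.* Secondary objectives expects caretakers' own resilience to gain, most in the group arm, and links those gains partly to more positive contact with youth. This makes a route to participants plausible, but it is not an admission that one exists.
- *The staff component is disclosed*, and the dissemination plan under Strengths includes employees. Roll-out without staff is therefore a possible misreading, not a stated plan.

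A reader might also infer that sharing staff training spoils the guided versus self-help contrast. The reverse is true: it holds the staff component constant, so that contrast better reflects facilitated delivery.

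None of this rescues the two phrases in {6b}. The sentence on TAU names the WebApp expressly. The sentence on standalone effectiveness follows directly from a remark on the resources that human support requires, so it will be read as meaning no staff input.

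**Conclusion.** The attribution in {6b} is wrong as written. Self-help versus TAU validly estimates the self-help WebApp plus trained and supervised staff, and its result cannot be assigned to the WebApp alone. The guided group versus TAU contrast is also a package effect, but there human support is part of the arm by design, so the point bears mainly on the second arm.

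The fault lies in attribution and wording. It is not a bias in the randomized comparison, nor an error in the model, the error rate or the power. The size of any staff effect is unknown. Staff training hours would not measure it, because hours of staff time say nothing about change in AFQ-Y.

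The conclusion assumes that staff training and supervision were delivered as Secondary objectives, {11c} and {15} describe. If TAU staff were trained before T3, as Table 1 could imply, the imbalance shrinks to supervision. If self-help caretakers received neither course nor supervision before T3, the concern falls away, and it is those descriptions that need correcting.

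**What to change.** 1. In {6b}, and wherever the rationale is repeated in the analysis plan and the results report, replace the claims of isolating the WebApp and of standalone effectiveness. State that both contrasts with TAU estimate the whole package.
2. Describe the second arm as self-help without a session facilitator, in institutions whose staff are START NOW-trained and supervised. 'Without guidance' may stay if it is defined as no facilitator in sessions.
3. Limit the conclusion on hypothesis 2 to that package and add the point to Limitations.
4. Reconcile Table 1 (two trained trainers in every institution) with Recruitment {15} (TAU training after follow-up II).
5. Report by arm which staff training and supervision were actually received before T3. If self-help caretakers received none, correct Secondary objectives and {11c} instead.

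Trial status says all participants are already in follow-up, so nothing in the conduct of the trial needs to change. The cost is some rewording and a table of staff inputs by arm. The downside is a narrower claim for the self-help arm.
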